## Background

Maternal and neonatal illness represent some of the most important health conditions in Uganda and in sub-Saharan Africa (SSA). Globally, of the 7.6 million deaths of children under five years each year [1], 3.6 million (41%) are deaths of babies in the neonatal period, and 98% of these deaths occur in developing countries. Although recent reports show some improvements in maternal mortality globally from the current estimate of 342,900 maternal deaths worldwide in 2008, down from 526,300 in 1980 [2], there has been minimal change in sub-Saharan Africa [2].

Most neonatal deaths, or death within the first month of life, take place on the day of delivery; between 30 and 50% of newborn deaths in Africa are on the first day of life, and 75% occur in the first week alone. The same is true for maternal deaths - approximately 50% of maternal deaths take place within one day of childbirth. A number of factors contribute to this high maternal and newborn mortality including the low (37%) skilled attendance at births, poverty, HIV/AIDS, low-quality antenatal and delivery care, and the unavailability of postnatal care on the continent, as most births occur at home due to problems related to inaccessibility to care.

Despite high use of antenatal care (ANC) (94% for the first ANC visit) in Uganda [3], deliveries at health facilities have remained low (42%), and Emergency Obstetric Care (EmOC) met need is only 14%. Postnatal care (PNC) coverage is very low and maternal mortality, perinatal and neonatal mortality have remained high (maternal mortality ratio 435 per 100,000 live births, perinatal mortality 36 per 1,000 and neonatal mortality 29 per 1,000 live births) [3].

To date, most efforts to improve maternal and newborn health in Uganda have focused on influencing the supply side, usually involving training of health workers, provision of supplies, and health education. Few interventions have been directed at influencing the community or the demand side. Previous efforts in safe motherhood and child health generally neglected newborn care, with the consequence that efforts to achieve Millennium Development Goal (MDG) 4 are currently greatly constrained by a relatively high proportion of neonatal deaths. In addition, focus has been on facility-based care with limited linkages between the facilities and the community.

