#### Dissemination phase

To inform on the design and scale-up of community-based mother-newborn care in Uganda.

**Hypothesis: H1:** Implementation of an integrated care package of five home visits by a CHW during pregnancy and the neonatal period to deliver one-on-one health messages and promote linkage to the health facility improves the following maternal-newborn care practices by at least 20% in two years amongst the target population in rural Uganda:

• % of pregnant women attending ANC at least four times (from 40% to 60%);

• % of pregnant women who get a skilled attendance at delivery (from 30% to 50%);

• % of mothers who put nothing on the cord (to get baseline figures during formative research);

•% of newborns who are managed in skin-to-skin contact after delivery (to get baseline figures during formative research);

• % of mothers and babies who receive postnatal care (from 12% to 50%).

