### Primary outcomes

1. In ANC

– % of pregnant women attending ANC two, four or more times

– % of pregnant women who know at least two danger signs of pregnancy

– % of pregnant women who prepare for birth

2. In the intrapartum period

– % of pregnant women who have a skilled attendant at delivery

– % of women who went to the HC in an emergency

3. In the postnatal period

– % of babies who are initiated on breast-feeding in the first six hours of birth

– % of babies who are exclusively breastfed during the neonatal period

– % of babies whose first bath was delayed for six and twenty-four hours

– % of mothers who put nothing on the cord

– % of mothers who know at least three neonatal danger signs

– % women whose children were managed in skin-to-skin contact after delivery.

– effectiveness of sepsis management (special studies to determine: maternal and CHW knowledge, compliance and timing of referral, and adequacy of treatment following referral)

Table 4 outlines in details all intermediate outcomes that will be evaluated in the study.

**Table 4 T4:** Study outcomes

**Area in the continuum of care**	**Outcome to be evaluated**

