	**NB. Analysis to be done separately for home and health facility births**
Antenatal care	• % of pregnant women attending ANC two, four or more times
	• % of pregnant women who know at least two danger signs of pregnancy
	• % of pregnant women who prepare for birth*
	• IPT in pregnancy
	• ITN use in pregnancy
	• Tetanus toxoid coverage
	• Uptake of VCT % of mothers who tested for HIV during pregnancy
	• Uptake of IPT - by number of doses
Intrapartum care	• % of pregnant women who have a supervised delivery
	• % of pregnant women who deliver at a health unit
	• % of babies whose cord was cut with a clean instrument
	• % of babies who are immediately dried at birth
	• % of babies who are immediately wrapped after birth
	• % of babies who are born on a clean surface
	• % of home births attended by two assistants
	• % of women who went to the HC in an emergency
Postnatal care	• % of babies whose cord was cut with a clean instrument
	• % of babies who are initiated on breastfeeding within one and twenty-four hours of birth
	• % of babies who are exclusively breastfed during the neonatal period
	• % of babies whose first bath was delayed for six and twenty-four hours
	• % of mothers who put nothing on the cord
	• % of mothers who know at least three neonatal danger signs
	• % of babies who are immediately dried at birth
	• % of babies who are immediately wrapped after birth
	• % of babies who are born on a clean surface
	• % of home births attended by two assistants
	• % women whose children were managed in skin-to-skin contact after delivery
	• mothers who received counselling regarding family planning by six weeks postnatally
	• % of babies who were taken for care if they were ill
	• % of babies referred to health facility by CHW that reach, and timeliness of reaching
Impact level	newborn deaths and stillbirths (note not powered to measure significant reduction in NMR) but we will explore each maternal and newborn death using the VASA and case–control study for, for example, intervention efficacy.
	Neonatal mortality rates will be calculated by intervention and comparison areas

*Birth preparedness will be operationalized through having made plans for where to deliver, transport, and preparing baby/delivery materials. IPT, intermittent presumptive treatment; ITNs, insecticide-treated nets; NMR, neonatal mortality rate; VASA, verbal and social autopsies; VCT, voluntary counselling and testing.

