### Additional analyses

GIS and socio-economic data are already being collected in the DSS and thus provide a good opportunity to undertake these analyses. In the control area, data analysis will also be done by doing a before-and-after comparison to estimate the effect of only health facility improvement on maternal and neonatal care facilities. Subgroup analyses estimating separate intervention effects for facility- and home-based deliveries.

Analysis will also be done taking account of the quality of the intervention received, as assessed by the process indicators and number of visits received. Because some study participants are highly mobile and some women will move from their place of residence to their parents’ or in-laws’ houses for delivery of the baby, it is envisaged that there may be significant movements across the arms of the trial (that is, some women will move from intervention to control areas and vice versa) during the intervention period. This movement can be tracked using our surveillance system. Thus we will also compare outcomes subdividing women and newborns into the following groups: whether the visits were only pre-delivery or only post-delivery or both, and whether the woman received all five visits, only four, three or two or less visits. However, the main analysis will be based on intention to treat so women who are enrolled in an intervention area, but move to a control area for delivery, will be included in the intervention group.

In addition, analysis will also be done of the mean practice score (a numerical outcome) will be carried out using random effects (multilevel) models that explicitly model the similarity between individuals in the same cluster; (these are not suitable for binary outcomes).

For all statistical determinations, significance levels will be established at 5% level of significance. Coefficient of variation will be reported.

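### Arm contrasts within home and facility births, and comparisons by visits received, condition on post-randomisation variables and should not be presented as intervention effects

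*Protocol article*

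**What the plan says.** Three places in the protocol article set up the splits.

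- **Table 4 (Study outcomes)** opens with the note "Analysis to be done separately for home and health facility births". It stands above the whole table and is not marked as secondary or limited to some outcomes. The same table lists the percentage "of pregnant women who deliver at a health unit" as an outcome.
- **Additional analyses** plans "Subgroup analyses estimating separate intervention effects for facility- and home-based deliveries".
- **Additional analyses** also compares outcomes for women and newborns by "whether the visits were only pre-delivery or only post-delivery or both", and by "whether the woman received all five visits, only four, three or two or less visits".

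The section on dissemination lists intervention differences by place of delivery among the findings to be published.

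Other sections bear on how to read this. Hypothesis H1 and Hypothesis testing set a target of 30% to 50% for skilled attendance at delivery. Home visits by CHWs describes the five visits as the core of the intervention, and Ethical considerations says a woman may decline them. Hypothesis testing defines the primary analysis of each outcome as intention to treat by village of residence, and Additional analyses repeats that the main analysis is intention to treat.

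**The concern.** Villages were randomised, so all births in intervention villages can be compared fairly with all births in control villages. That does not carry over to subsets defined by something that happens later and that the intervention changes.

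If the package works as hoped, some women who would have delivered at home deliver in a facility instead. Home births in the intervention arm then lack these women, and facility births in that arm include them. In the control arm it is the reverse. The two arms' home births, and likewise their facility births, are different kinds of women even if the package does nothing to the practice being compared.

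Visit counts have a related problem. Women who accept all five visits, or who stay in the village to receive them, probably differ from those who do not, and part of the count accrues after some of the outcomes.

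At stake is a set of published place-of-delivery effects and an apparent dose-response, in a trial meant to inform national scale-up.

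**Working it through.** The plan gives no figure for these analyses, so there is none to reproduce. What follows shows how large the selection can be.

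**1. Place of birth**

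Inputs from the protocol: skilled attendance 30% under control and 50% under intervention. The protocol says deliveries are allowed only from health centre level III upward, so skilled attendance is a reasonable proxy for facility birth, but only a proxy.

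This gives three groups of women, if nobody is moved from facility to home:
- always facility, A = 0.30
- moved from home to facility by the intervention, C = 0.20
- always home, N = 0.50

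Let the rates of some practice be a, c and n in these groups (assumed; the protocol gives none), identical in both arms, so the true effect is zero.

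- Facility births: control a; intervention (A·a + C·c)/(A + C). Difference = -0.4 × (a - c).
- Home births: control (C·c + N·n)/(C + N); intervention n. Difference = -(2/7) × (c - n).

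With a, c, n = 0.80, 0.60, 0.40:
- all births, both arms: 0.30×0.80 + 0.20×0.60 + 0.50×0.40 = 0.56, difference 0
- facility births: 0.80 v (0.24 + 0.12)/0.50 = 0.72, difference -8.0 points
- home births: (0.12 + 0.20)/0.70 = 0.457 v 0.40, difference -5.7 points

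Other assumed rates:

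| a / c / n | Facility difference (points) | Home difference (points) |
|---|---|---|
| 0.50 / 0.40 / 0.30 | -4.0 | -2.9 |
| 0.60 / 0.45 / 0.30 | -6.0 | -4.3 |
| 0.70 / 0.50 / 0.30 | -8.0 | -5.7 |
| 0.80 / 0.55 / 0.30 | -10.0 | -7.1 |
| 0.60 / 0.30 / 0.30 | -12.0 | 0 |
| 0.60 / 0.60 / 0.30 | 0 | -8.6 |
| 0.50 / 0.50 / 0.50 | 0 | 0 |

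A real benefit can also be masked. Take 0.70 / 0.50 / 0.30 and add a true 10 points for every woman in the intervention arm:
- facility births: (0.30×0.80 + 0.20×0.60)/0.50 - 0.70 = +2.0 points
- home births: 0.40 - 0.25/0.70 = +4.3 points

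**2. Outcomes that cannot be split this way**

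Delivery at a health unit is 100% among facility births and 0% among home births by definition. The antenatal rows of Table 4 (ANC attendance, tetanus toxoid, HIV testing) are settled before the birth, so the split conditions them on a later event.

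**3. Visits received**

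A simulation of 2,000,000 women had no effect of visits on the practice. An unmeasured care-seeking tendency u (standard normal) raised both the number of visits, binomial out of 5 with logit 0.5 + b·u, and the practice, with logit -0.4 + b·u. All these values are assumed.

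| Tendency b | Practice rate, 2 or fewer visits | Practice rate, 5 visits |
|---|---|---|
| 0.25 | 0.38 | 0.43 |
| 0.50 | 0.34 | 0.50 |
| 1.00 | 0.26 | 0.63 |

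A dose-response appears although visits do nothing.

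Timing adds to this. Table 1 places three of the five visits after birth, so they cannot have influenced ANC attendance or where and with whom the woman delivered. The lowest category also pools women with no visit with those who had one or two.

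**The case against.** The strongest reply is that the trial's main inference is already safe. The primary analysis of each outcome is unsplit intention to treat by village, both splits appear under Additional analyses, and the hypotheses under Hypothesis testing depend on neither. Table 4 holds rows that cannot sensibly be split, so its note is probably meant as an addition to the main comparison. This stands as far as it goes. A reader might infer from the note that the primary effect estimates are themselves biased, and the article does not support that. It does not rescue the splits, though: the note does not say it is secondary, and Additional analyses says outright that intervention effects will be estimated within strata.

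It is also fair to say that the sizes above rest on assumed rates and a proxy. They show what is possible; they do not predict what this trial will find.

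Other stronger readings are tempting and should not be pressed:

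- **Five visits will look protective against death by construction.** The Background says of newborn deaths that "75% occur in the first week alone", and a baby who dies before the third postnatal visit cannot have had five. But Additional analyses does not name mortality for the visit comparison, Table 4 specifies mortality by area, and the first-week figure includes deaths on days 5 to 7, when that visit may already have taken place.
- **Postnatal visits come too late to affect the first bath.** Table 1 allows the first postnatal visit on the day of birth and lists delayed bathing among its tasks, and the outcome includes delay to twenty-four hours.
- **The emergency outcome is conditional on a recognised emergency.** The article says only the percentage "of women who went to the HC in an emergency" and does not state the denominator.
- **Allocation could serve as an instrument for visits.** Intervention villages also had sensitisation meetings and community-facility linkage with supervision, so allocation need not act through visits alone.

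**Conclusion.** The point holds for the secondary analyses. Arm contrasts within home and facility births, and comparisons by visits received, can be biased by selection and should not be presented as intervention effects. With a 20-point shift in place of birth and the main assumed rates, the false differences are about -6 points (home) and -8 points (facility). Across the graded scenarios they run from -2.9 to -7.1 and from -4 to -10. If the ordering of rates were reversed, the sign would reverse. The facility bias is zero only if the moved women match those they join, and the home bias only if they match those they leave. Separately from any assumption, the Table 4 note cannot apply to delivery at a health unit, and it splits antenatal outcomes by a later event. The primary intention-to-treat comparison is unaffected.

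**What to change.** - Replace the Table 4 note with a statement that, for every outcome, the effect estimate is the unsplit intention-to-treat comparison among all births by village of residence, and that results by place of birth are descriptive with no intervention effect claimed. The row on home births with two assistants is confined to home births by definition, so it belongs with the descriptive results.
- Under Additional analyses, delete the plan to estimate separate effects for facility and home deliveries. Bring the dissemination list into line.
- Label the comparisons by number and timing of visits exploratory and non-causal. Count only visits that precede the outcome: pregnancy visits alone for ANC attendance and for place of, or attendance at, birth. Separate zero visits from one or two.
- If deaths are ever compared by visit count, start follow-up at a landmark after the last of the five scheduled visits. Earlier deaths then drop out of that comparison.

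This changes wording only, with no change to sample or field procedures, and can be carried into the detailed analysis plan that the article says is still to be finalised. The price is that no stratum-specific effect can be claimed.

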**Postnatal visit 2: day 3 after birth**	
●	Assess for maternal and newborn danger signs and refer if necessary
●	Refer for immunization
●	Counsel mother on breastfeeding and birth spacing
●	Reinforce need to seek care/call CHW for signs of local infection or danger signs

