**Postnatal visit 3: day 5 to 7 after birth**	
●	Assess for maternal and newborn danger signs and refer if necessary
●	Refer for immunization
●	Counsel mother on breastfeeding and birth spacing
●	Reinforce need to seek care/call CHW for signs of local infection or danger signs
●	Promote access to under five clinics and family planning at six weeks
**If very low birth weight suspected**^**1**^	
●	Refer if also danger sign present or two extra visits to support home care (breastfeeding, warmth, early danger sign recognition) if no danger sign or referral not possible
●	Promote temperature management (skin-to-skin, wrapping and delayed bathing)
●	Assist with feeding if needed
●	Attention to hygiene

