### Data collection for quantitative surveys

The DSS data collection and recording system will be used. This is a comprehensive system in which all households have been mapped and given a unique number. All members of each household are known. Each village has a trained data collector and every five to six field assistants have a field supervisor and a local community key informant. A team of local enumerators have already mapped the 18 parishes using geographical information systems (GIS), identified and allocated a unique identification number to every household (defined as a group of individuals sharing one kitchen), did a baseline census of demographic and socio-economic indicators, and generated a list of female household members according to predefined written protocols. During the thrice-yearly update rounds questions are asked of all females 12 to 50 years of age, whether they are pregnant and approximate age of the pregnancy estimated. This pregnancy registration is then followed up in the next update round for birth outcome. In addition, community key informants report births to the DSS staff.

Repeated surveys of practices are done twice per year. Each survey takes some three months to complete. Based on pregnancy recording from the DSS round and birth reports by community key informants at the estimated end of the neonatal period, a field worker will visit the woman to interview on practices during pregnancy, delivery and the first month of life. The interview will include details of any preceding pregnancy, home-care practices, exposure to the CHW home visits, and use of health services for neonatal illness. The questionnaires will be written in English and translated into the local language, Lusoga, and the accuracy of the translation will be checked by back translation into English. Medical experts will review the questionnaire for content validity. Interviewers will administer the survey in Lusoga, the local language. The survey will be pilot tested among 20 mothers outside the DSA and the resulting suggestions regarding clarity and cultural appropriateness will be incorporated.

Field editing will be done. After correction, data will be double-entered into a relational database management system.

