While not a primary outcome, variable stillbirth rate and neonatal mortality rate will be followed through the study in both intervention and control areas. We will define miscarriage as cessation of a presumptive pregnancy before 28 weeks of gestation and stillbirth as fetal death after 28 weeks of gestation but before delivery of the baby’s head, which was a modification of the 22-week definition to meet local practicalities. We will classify neonatal death as death of a live born infant within 28 completed days of birth. Early neonatal deaths will refer to deaths within 7 completed days after delivery. Separate analysis will be done for neonatal mortality excluding the first day of life in order to assess the role of sepsis.

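### The outcome of family planning counselling by six weeks cannot be measured by the interview described, which covers only about the first four weeks after birth

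*Protocol article*

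**What the plan says.** Table 4 (Study outcomes, postnatal care rows) includes "mothers who received counselling regarding family planning by six weeks postnatally". The text before the table presents it as the full list of intermediate outcomes to be evaluated.

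The section on data collection for quantitative surveys describes one interview with mothers about practices. On timing it says that "at the estimated end of the neonatal period, a field worker will visit the woman to interview on practices". On content it says the worker will "interview on practices during pregnancy, delivery and the first month of life". The same section adds "Repeated surveys of practices are done twice per year" and "Each survey takes some three months to complete". The section on additional analyses defines neonatal death as "death of a live born infant within 28 completed days of birth", which fixes the length of the neonatal period.

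Table 1 gives the CHW home visits, which take place in intervention villages only. Postnatal visit 2 (day 3) includes "Counsel mother on breastfeeding and birth spacing", and the same line appears at visit 3 (days 5 to 7). Visit 3 also includes "Promote access to under five clinics and family planning at six weeks".

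**The concern.** The outcome has a window of six weeks, but the interview that would supply it is placed at about four weeks and looks back over the first month. A mother counselled in week five or six has not yet been counselled when she is asked. Followed as written, the plan would report counselling by about 28 days under a six-week label.

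The missing part of the window may not fall equally on the two arms. Intervention mothers have a source of advice in the first week, which the interview can see. Counselling at a six-week contact, in either arm, it cannot see. The reported arm difference would then not be the difference by six weeks, and a reader of the results could not tell which way it was off.

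**Working it through.** The plan gives no figure for this outcome, so there is none to reproduce. The check compares windows and then asks what can be said about direction.

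**1. Window against recall**

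- Outcome window (Table 4): six weeks = 6 × 7 = 42 days.
- Interview (data collection section): end of the neonatal period, 28 days by the definition under additional analyses.
- Not covered: 42 − 28 = 14 days; 14/42 = 33%.
- If the first month is read as 30 or 31 days, the gap is 12 or 11 days, still 29% or 26% of the window.
- The six-week point named at postnatal visit 3 in Table 1 lies in the uncovered part on every reading.

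**2. Direction of the error in the arm difference**

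Let e be the proportion counselled by day 28. Let c be the proportion, among those not yet counselled, who are counselled between day 28 and day 42. Subscripts i and c denote intervention and control.

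- Difference seen at day 28: e_i − e_c.
- Difference by six weeks: (1 − e_c)(1 − c_c) − (1 − e_i)(1 − c_i).
- Error (seen minus six-week): (1 − e_c)c_c − (1 − e_i)c_i.

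The error favours the intervention only if c_i/c_c is below (1 − e_c)/(1 − e_i). The documents give none of these four quantities, so the following values are assumptions chosen only to show the behaviour: e_i = 50%, e_c = 5%, c_c = 20%. The seen difference is 50 − 5 = 45 points, and the error is 0.95 × 0.20 − 0.50 × c_i = 0.19 − 0.50 c_i.

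| c_i (assumed) | Seen at day 28 | By six weeks | Error |
|---|---|---|---|
| 20% | 45 points | 36 points | overstated by 9 |
| 30% | 45 points | 41 points | overstated by 4 |
| 40% | 45 points | 46 points | understated by 1 |
| 60% | 45 points | 56 points | understated by 11 |

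The sign changes at c_i/c_c = 0.95/0.50 = 1.90. With e_i from 30% to 70% and e_c from 5% to 12% (also assumed), the turning point runs from 0.88/0.70 = 1.26 to 0.95/0.30 = 3.17.

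The gap in the window is therefore fixed by the text, but the sign of its effect on the arm comparison is not.

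**The case against.** The strongest reply is that the interview timing is looser than it looks. The phrase about the end of the neonatal period can be read as timing the key informants' birth reports rather than the visit, and a survey that takes three months may reach some mothers well after day 28. The topics listed for the interview need not be exhaustive. Other sources exist: annual coverage surveys under randomization, and household surveys, facility surveys and facility registers under process documentation. A journal article may also leave questionnaire items to the full protocol.

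Part of this stands: some mothers may be interviewed late, and the article does not rule out another source. It does not remove the conflict. The stated recall content still ends at the first month, and nothing ties another source to this outcome. If visits do drift, some women would be asked before six weeks and others after, so the item would mean different things for different women. Both the window and the interview are stated in the article, so this is a conflict between two statements and not an omitted detail.

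A reader might go further and infer that the early interview biases the comparison towards the intervention, since first-week CHW advice is counted and later clinic counselling is cut off. The documents do not support that, for three reasons:

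- CHWs promote family planning access at six weeks in intervention villages only, so the interview also misses a contact that the intervention is meant to raise.
- No section gives control mothers a scheduled six-week family planning contact, and facility strengthening covers both arms.
- Counting birth spacing advice as family planning counselling is a reasonable inference, but Table 1 lists the two as separate items, and the questionnaire is not shown.

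**Conclusion.** The point holds as a mismatch between outcome and measurement. As described, the interview leaves about 14 of 42 days unobserved, including the six-week point, so it cannot supply an outcome defined by six weeks. This rests on taking the neonatal period as 28 days, on the stated recall period, and on the absence of any other source linked to this item.

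Under-ascertainment may differ between arms. Neither its direction nor its size can be derived from the documents, and the table of assumed values shows that both signs are possible. No inflation figure should be quoted.

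The weight is limited. This is one of about 30 lines in Table 4. It is not in the primary outcome list, is not among the stated hypotheses and does not drive the sample size, so the trial's main conclusions do not depend on it.

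**What to change.** Reconcile Table 4 with the data collection section in one of two ways:

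- **Rename the outcome** as family planning counselling by the end of the neonatal period (28 days), and draw no conclusion about six weeks. This is one line in Table 4 and costs no fieldwork, but the trial then says nothing about weeks five and six.
- **Ask this item at or after day 42 in both arms**, with the recall period stated to run to six weeks. If the whole interview moves, birth practices are recalled about two weeks later than planned. If only this item moves, a further contact is needed.

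Under either choice, state whether birth spacing advice from a CHW counts as family planning counselling.
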